## Abstract

**Background:**

Cerebral palsy leads to many complications as well as delayed motor development, and early intensive rehabilitation in infancy, which is based on the theory of brain plasticity, is emphasized. In addition to conventional treatment, including physical, occupational, or speech-language therapies, children also have a demand for traditional Korean medicine interventions such as acupuncture or herbal medicine; however, a lack of evidence has made traditional Korean medicine difficult to implement in practice. We planned a multicentre, prospective, observational study to assess the effectiveness, safety and cost-effectiveness of conventional treatment and traditional Korean medicine combination treatment for children with cerebral palsy.

**Methods/Design:**

Three hundred children with cerebral palsy aged 6 to 78 months will be recruited from six institutions. Data from each child are collected every month for a one-year period, during which time treatment might be changed or discontinued. A qualified investigator visits the sites to measure effectiveness variables, including Gross Motor Function Measure and Paediatric Evaluation of Disability Inventory. Adverse events and cost-effectiveness variables are collected using surveys conducted at baseline, mid-study, and end of study, as well as monthly tracking surveys. In the analyses, participants will be classified into two groups: group A children will be the conventional treatment group with physical, occupational, speech-language or other conventional rehabilitation therapies, whereas group B children will be the combination treatment group with traditional Korean medicine interventions, that is, herbal medicine, chuna, moxibustion and acupuncture, in addition to conventional treatment.

**Discussion:**

Only a few clinical case reports have evaluated the effectiveness and safety of traditional Korean medicine; therefore, more data are required to provide optimal information to children with cerebral palsy and their guardians. We hypothesized that traditional Korean medicine combination treatment for children with cerebral palsy would have benefits compared with conventional therapy alone. The findings of this study might provide informative data for conducting economic evaluations and developing clinical research on combination treatment for cerebral palsy in South Korea.

**Trial registration:**

NCT02223741

## Background

Cerebral palsy (CP) describes a group of disorders of the development of movement and posture that cause activity limitations; these disorders are attributed to non-progressive disturbances that occur in the developing foetal or infant brain [1]. Although the main feature of CP is a movement disorder, difficulties with cognition, learning, communication and behaviour often accompany CP. To manage these complicated situations, integrative therapies for rehabilitation have been developed and applied in practice [2]. From a systematic review of 49 studies, the pooled overall prevalence of CP was 2.11 per 1000 live births [3]. The prevalence of CP is 2.6 per 1000 children, and the attributable lifetime cost of CP is approximately 1.8 times higher than the basic lifetime medical cost of the general population in South Korea [4].

Intensive rehabilitation for young children is predicted to give potential benefits in terms of brain plasticity. Neuronal plasticity is enhanced in the developing brain, and it is usually adaptive and beneficial for neurological disorders such as CP. Clinical examples of adaptive neuronal plasticity include reorganization of cortical maps of the fingers in response to practice playing a stringed instrument and constraint-induced movement therapy to improve hemiparesis caused by CP [5].

In general, interventions include not only surgery or botulinum toxin for the inhibition of spasticity but also physical therapy (PT), occupational therapy (OT), speech therapy (ST), hydrotherapy, and other therapies [6]. Although there are public demands for complementary and alternative medicine (CAM) for children with CP, the lack of evidence makes alternative medicine difficult to implement in practice [7].

In a systematic review of traditional Chinese medicine (TCM) for children with CP, the authors concluded that a combination of either acupuncture plus chuna or acupuncture plus herbal medicine with conventional therapy showed significant beneficial effects on comprehensive function in terms of both physical and cognitive aspects, independence, and verbal function compared with conventional therapy alone [8]. Additionally, a rehabilitation approach including acupuncture that was intensely administered to young children with spastic CP resulted in significant functional improvement [9].

In Korea, children usually receive conventional treatment, including physical, occupational, or speech-language therapies, and they also have a demand for traditional Korean medicine (TKM) interventions such as acupuncture or herbal medicine. We now aim to investigate the effectiveness, safety, and cost-effectiveness of both conventional and TKM combination treatment for children with CP.

## Methods/Design

### Study design

The study team is conducting a one-year, multi-site, prospective observational study of rehabilitation for children with CP. We are recruiting the children at two university-affiliated hospitals, one TKM hospital and three TKM clinics. The children with CP receive treatments from doctors and therapists in each clinic or centre, and one independent investigator assesses functional changes in participants and collects survey documents from their guardians or parents. We will analyse changes in the children’s functional development and health condition, the number of adverse events, and monetary resources spent for rehabilitation during this period. This design is a comparative observational study of a conventional treatment group and a TKM combination treatment group (Fig. 1).

**Fig. 1 Fig1:**
[figure not shown]
Observational study concept diagram. GMFM-66, Gross Motor Function Measure-66; QALYs, quality-adjusted life years

### Participant eligibility

The study subjects are children with CP aged 6 to 78 months. Because the Paediatric Evaluation of Disability Inventory (PEDI) assessment module is suitable for children under the age of seven, we defined the upper age criterion considering the one-year follow-up period. Children who have had orthopaedic surgery due to CP; children who have congenital muscular disease, hereditary disease, or progressive central nervous system diseases; and children who suffer from severe diseases (i.e., cancer, severe heart disease, or severe infectious disease) are excluded from this study.

### Consent and registration

The subjects are being recruited from hospitals and local clinics specializing in CP. The children’s guardians provide consent to the enrolment because children under the age of seven cannot provide voluntary agreement. After the guardians are provided with study information leaflets, they have the opportunity to ask questions concerning the study. They are assured that participation or non-participation in the study will not affect the clinical care their children receive. Once informed consent is obtained, eligibility criteria are evaluated, and the central research group assigns each eligible participant an identification number. Registration of this study will be closed when the planned number of participants has been reached.

### Treatment

The participants undergo rehabilitation according to their doctors’ clinical care, but they do not receive any intentional treatments. During the period, they can freely start, cease or change any conventional treatments or TKM treatments. The conventional treatments can include PT, OT, ST and other conventional therapy, and the TKM treatments include herbal medicine, chuna, moxibustion and any type of acupuncture, e.g., body acupuncture, scalp acupuncture and pharmacopuncture. The most frequent set of TKM treatments implemented for CP children in South Korea is acupuncture and/or herbal medicine.

### Data collection

Data are obtained by participant survey and investigator measurement at baseline and at specified follow-up times (Table 1).

**Table 1 Tab1:** Schedule of observations

	Screening	Registration	Observation period											
Study month (month)		baseline	1	2	3	4	5	6	7	8	9	10	11	12
Visit number	−1	1						2						3
Visit windows (week)							26 ± 1						52 ± 1	
Informed consent	●													
Demographics	●													
Medical history	●													
Inclusion/exclusion criteria	●													
Height		●						●						●
Weight		●						●						●
Concomitant disorders		●						●						●
Health problems		●						●						●
Survey														
Medication		●	●	●	●	●	●	●	●	●	●	●	●	●
Conventional treatment		●	●	●	●	●	●	●	●	●	●	●	●	●
TKM treatment		●	●	●	●	●	●	●	●	●	●	●	●	●
Health supplements		●	●	●	●	●	●	●	●	●	●	●	●	●
Medical care cost		●	●	●	●	●	●	●	●	●	●	●	●	●
Quality of life		●	●	●	●	●	●	●	●	●	●	●	●	●
Adverse events		●		●	●	●	●	●	●	●	●	●	●	●
Assessment														
GMFCS		●						●						●
GMFM-66		●						●						●
PEDI		●						●						●

●: assessment and observation will be performed

*TKM* traditional Korean medicine, *GMFCS* Gross Motor Function Classification System, *GMFM-66* Gross Motor Function Measure-66, *PEDI* Paediatric Evaluation of Disability Inventory

#### Participant survey

Parents or guardians respond to survey questionnaires. Data are collected using surveys conducted at baseline, mid-study, and end of study, and monthly tracking surveys will also be used. A baseline interview survey consists of basic characteristics, cause of CP, concomitant disorders, health problems, surgical history, medication, rehabilitation therapies, TKM treatment, health supplements, and medical care cost. An interview survey conducted on the 26th and 52nd weeks will include questions on concomitant disorders and health problems. The monthly tracking survey obtains information on health problems, changes in rehabilitation and treatments, medical care cost, and quality of life (QOL) with the Peds-QL CP module (ver 3.0) [10]. These guardian-reporting documents are collected and managed by the Clinical Research Center of Pusan Korean Medicine Hospital each month for a year. After the parents or guardians complete the forms, the investigators ensure that there are no blank spaces. In the case of insufficient data, we will check the accuracy of the information by reviewing medical records.

We will translate the PedsQL CP module (ver 3.0) into a Korean version and perform concurrent validation and reliability studies.

#### Investigator assessment

A qualified investigator visits the sites to measure each participant’s height and weight and classify each child according to the Gross Motor Function Classification System (GMFCS). The investigator is not a treatment provider nor an employee of any hospital or clinic, and this constitutes unbiased evaluation.

Gross motor function is assessed using the Gross Motor Function Measure-66 (GMFM-66) and the PEDI. All measurements and assessments will be performed at baseline and at the 26^th^ and 52^nd^ weeks. In this study, we will use the Korean versions of the GMFCS [11], GMFM-66 [12], and PEDI [13], which have undergone validity and reliability studies [14].

### Primary outcome measurement

The first primary outcome is the changes from baseline of the GMFM-66 scores at weeks 26 and 52. The GMFM-66 includes 66 items identified through Rasch analysis, which collectively best describe gross motor function in children with CP of varying abilities [15, 16]. The second primary outcome is the changes from baseline of the PEDI scores at weeks 26 and 52. The PEDI uses 217 questions to measure abilities in the three functional domains of self-care, mobility and social function [17].

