### Rationale for sample size

The sample size was determined on the basis of the primary outcome measure, GMFM-66. Using a 2-sided test, a sample size of approximately 37 children per treatment would assure 80 % power to detect a difference of at least 1.6 points (α = 0.05) assuming a standard deviation of 2.2 and dropout rate of 0.2. This mean change of 1.6 points in GMFM-66 scores was considered a clinically meaningful change in previous studies [17, 19]. We also planned the sub-group analyses considering disease severity measured by GMFCS (2 sub-groups, I-III and IV-V) and age (2 sub-groups, <3 and ≥3) heterogeneity. Therefore, a total of 300 participants will be required.

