**Fig. 2 Fig2:**
[figure not shown]
Process and time line of the observational study. CT, conventional treatment; TKM, traditional Korean medicine; ATx, acupuncture; Mx, medication

For the analysis of effectiveness, multiple variables, including age, severity of illness (indicated by the GMFCS), and treatments, will be converted to propensity scores by logistic regression, and the two groups will be compared by matching or stratification. We expect that using propensity scores will enhance the control variables of heterogeneous conditions. The last observation carried forward method will be used to handle missing data. The change from baseline of the GMFM-66 and PEDI scores at weeks 26 and 52 will be representative outcomes to evaluate effectiveness. These outcomes will be analysed by a two-sample *t*-test for the cross-sectional dataset and by a linear mixed model for the longitudinal dataset [20].

For sub-group analysis, we will analyse the correlation between rehabilitation intensity and functional changes in each group. We will also examine the different outcomes between acupuncture and acupuncture plus herbal medication cases in the TKM combination treatment group.

The number of participants with SAEs and non-SAEs will be reported via analysis of frequency, and the detailed progress of SAEs and related health problems will be disclosed as safety issues. In the case of long-term medication, we will carefully investigate adverse drug reactions using the drug-induced liver injury causality assessment scale [21].

The effectiveness of TKM reported by guardians will be used for further patient-centred outcome research. In the case of participants ceasing TKM treatments, we will investigate the reasons to enhance the feasibility of developing an RCT protocol.

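### GMFM-66 and PEDI are both primary at both weeks, with no contrast named as deciding, while the sample size rests on one GMFM-66 contrast with no stated week

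*Protocol article*

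**What the plan says.** Under Primary outcome measurement, the protocol article lists two primary outcomes, each at two visits: "The first primary outcome is the changes from baseline of the GMFM-66 scores at weeks 26 and 52" and "The second primary outcome is the changes from baseline of the PEDI scores at weeks 26 and 52". It describes PEDI by its domains, "The PEDI uses 217 questions to measure abilities in the three functional domains of self-care, mobility and social function", and does not say which PEDI score is the primary one.

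Under Statistical and analytical plans, both outcomes at both visits have the same standing: "The change from baseline of the GMFM-66 and PEDI scores at weeks 26 and 52 will be representative outcomes to evaluate effectiveness". They go to a two-sample t-test for a cross-sectional dataset and to a linear mixed model for a longitudinal one. The same section allows the treatment groups to be defined on either six months or one year of follow-up.

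Under Rationale for sample size, the outcome is singular: "The sample size was determined on the basis of the primary outcome measure, GMFM-66". The calculation gives "Using a 2-sided test, a sample size of approximately 37 children per treatment" for "80 % power to detect a difference of at least 1.6 points (α = 0.05) assuming a standard deviation of 2.2 and dropout rate of 0.2". This is the only place where a significance level appears, and no week is attached to the difference of 1.6 points.

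**The concern.** Two outcomes at two weeks make four primary comparisons of combination treatment with conventional treatment. The sample-size section relies on one comparison at two-sided 0.05, and the outcome and analysis sections do not say which of the four that is.

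The four can disagree. PEDI could favour combination treatment at week 26 while GMFM-66 shows nothing at week 52, and the text has no rule for what the study then concludes. The choice could be made after the data are seen. This matters because the Discussion states a directional hypothesis of benefit and raises the possibility of promoting combination treatment in a guideline.

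**Working it through.** **1. Reproduce the plan's figure.** Inputs from Rationale for sample size: difference 1.6, SD 2.2, two-sided alpha 0.05, power 80%, dropout 0.2.

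n per group = 2 × (1.960 + 0.842)² × (2.2/1.6)² = 29.7. Allowing for dropout, 29.7/0.8 = 37.1, which matches the stated 37 (rounding up to 30 first gives 38). With two treatments and the four severity-by-age cells, 37 × 2 × 4 = 296, close to the stated 300. The size therefore fits one contrast at the full 0.05. At two-sided 0.025 the same formula gives 44.9 with dropout, so no split of alpha is built in.

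**2. Count the contrasts.** 2 outcomes × 2 weeks = 4, taking PEDI as one score. If GMFM-66 and three PEDI domains were each tested, 4 × 2 = 8. The article does not say that the domains are tested separately, so four is the count that the text supports.

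**3. Error rates if any one result suffices and nothing is adjusted.** Two quantities must be kept apart: any false significant result (5% for one test), and a false result favouring TKM (the favourable tail only, 2.5% for one test).

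Independent tests:
- Four contrasts, either direction: 1 − 0.95⁴ = 18.5%.
- Four contrasts, benefit only: 1 − 0.975⁴ = 9.6%. Whatever the correlation, this cannot exceed 4 × 2.5% = 10%.

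The article gives no correlations. The range assumed is 0 to 0.7 between outcomes and 0 to 0.8 between weeks. Results from 1,000,000 simulated sets of correlated normal test statistics with a critical value of 1.96 (first row by formula):

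| Correlation between outcomes | Correlation between weeks | Any false significant result | False claim of benefit |
|---|---|---|---|
| 0 | 0 | 18.5% | 9.6% |
| 0.3 | 0.3 | 17.7% | 9.0% |
| 0.5 | 0.5 | 16.2% | 8.1% |
| 0.5 | 0.7 | 14.9% | 7.5% |
| 0.7 | 0.8 | 12.8% | 6.5% |

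Against one test, this is 12.8/5 = 2.6 to 18.5/5 = 3.7 times in either direction, and 6.5/2.5 = 2.6 to 9.6/2.5 = 3.8 times for benefit.

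**4. Eight contrasts, for comparison only.** Either direction: 19.6% to 33.7%, where the upper end is 1 − 0.95⁸. Benefit only: 9.8% to 18.3%, where the upper end is 1 − 0.975⁸.

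**The case against.** The strongest reply is that this is a condensed article on an observational study, and that multiplicity rules commonly sit in a full protocol or analysis plan that is not shown. Ranking a first and a second primary outcome and sizing on the first is ordinary practice, and the singular wording in the sample-size section may only be loose.

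Much of that stands. The absence of an alpha split is not in itself an error in this article. What remains is what the article does fix: two outcomes at two weeks with equal standing, and a size calculation for one contrast that the other sections do not identify. First and second are labels; nothing makes them a testing order. Which outcome and week are primary belongs in the protocol, and an unseen analysis plan would leave these sections unaligned.

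A reader might infer more than the text supports:

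- **That each contrast is tested at the full 0.05.** Alpha is stated only for the GMFM-66 sample size. The article states no adjustment, which is a weaker fact.
- **That any one success is enough.** No section says so. If all four had to succeed there would be no inflation. In that case the size would be unsupported for another reason, since it gives no PEDI difference or SD.
- **That a false claim of TKM benefit is three to five times 5%.** With four contrasts it is at most 10%, twice 5%. Ratios of about three hold for benefit only against 2.5%, and a ratio of five needs the eight-test count.
- **That the t-test and the mixed model are two attempts at the same contrast.** They are assigned to different datasets, so they are not counted here as extra tests.

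**Conclusion.** The concern holds as an unresolved choice of primary contrast. The outcome and analysis sections give at least four primary contrasts and none that decides, and the sample-size section supports one GMFM-66 contrast with no week.

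The size is conditional. With an any-one-wins rule, no adjustment, the assumed correlations, PEDI as a single score and no confounding bias in this non-randomised comparison, at least one false significant result occurs in about 13% to 19% of studies instead of 5%. A false claim of TKM benefit occurs in about 6.5% to 10% instead of 2.5%. Separate testing of the PEDI domains would raise both, but the article does not state that it is planned.

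**What to change.** - **Primary outcome measurement and Rationale for sample size:** name the same deciding contrast in both. It should be GMFM-66 change at one named week, at two-sided 0.05, so that it agrees with the calculation already made. Week 52 is one example; nothing in the article forces that choice.
- **Statistical and analytical plans:** name the one analysis that supplies this contrast and label the other supportive. State whether six months or one year of follow-up defines the treatment groups for it, because otherwise one named week could still have two group definitions.
- **Remaining outcomes:** test GMFM-66 at the other week and one named PEDI score (or its domains) in a fixed order, each at 0.05, stopping at the first non-significant result. If PEDI is to stay co-primary, use Holm over GMFM-66 and one named PEDI score instead.

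The cost is wording, with no extra children or visits. The fixed order keeps the full 0.05 for GMFM-66, so the figure of 37 is unaffected. Under Holm the first step is at 0.025, which on the same inputs needs about 45 per group with dropout. The scientific price of the fixed order is that a significant PEDI or other-week result standing alone can no longer be claimed as a primary success.

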### Secondary outcome measurement

The secondary outcomes involve safety and cost-effectiveness (utility) analysis components. One secondary outcome will be the number of participants with serious adverse events (SAEs) and non-SAEs during the study period. Cost data include direct medical and non-medical costs, indirect costs and productivity losses. Utility scores (EQ-5D) will be estimated from the mapping equation of PedsQL developed by Khan et al. [18], and then will be used for calculating quality-adjusted life years (QALYs) based on the area under the curve method. Cost-utility analysis will be conducted from a societal perspective, which includes direct medical costs, direct non-medical costs, and indirect non-medical costs measured as productivity loss of parents and other caregivers.

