### Statistical and analytical plans

The study will present both descriptive and comparative results of conventional treatment and TKM combination treatment. In this study, we define operationally the conventional treatment (CT) group as children who have received only PT, OT, ST, and other conventional therapies, whereas the TKM combination treatment (CT + TKM) group is defined as children who have received at least twelve sessions of any type of acupuncture or 30 days of herbal medication within a 6-month follow-up period in addition to conventional therapies. At the time of analysis, participants will be classified in the conventional or TKM combination treatment group based on the six-month or one-year follow-up information (Fig. 2).

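### Safety is framed as a number of events in one section and as children affected in two others, and the per-child count allows neither for unequal follow-up nor for when TKM began

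*Protocol article*

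**What the plan says.** Three places in the protocol article describe the safety quantity.

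- **Study design** lists among the things to be analysed "the number of adverse events, and monetary resources spent for rehabilitation during this period". The unit is the event.
- **Secondary outcome measurement** states: "One secondary outcome will be the number of participants with serious adverse events (SAEs) and non-SAEs during the study period". The unit is the child.
- **Statistical and analytical plans** (the safety paragraph after Fig. 2) repeats the child as unit and names the method: "The number of participants with SAEs and non-SAEs will be reported via analysis of frequency".

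Four other statements determine how such a count behaves.

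- **Treatment**: "During the period, they can freely start, cease or change any conventional treatments or TKM treatments".
- **Statistical and analytical plans**: "participants will be classified in the conventional or TKM combination treatment group based on the six-month or one-year follow-up information".
- **Rationale for sample size**: a dropout rate of 0.2 is assumed.
- **Abstract, Methods/Design**: "Adverse events and cost-effectiveness variables are collected using surveys conducted at baseline, mid-study, and end of study, as well as monthly tracking surveys". Table 1 marks adverse events at baseline and at months 2 to 12, and TKM treatment at baseline and every month.

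**The concern.** Number of events and number of children with an event are different outcomes. One child with six events adds six to the first and one to the second, so the two can rank the groups differently. Safety is one of the study's three stated aims, so its unit should not depend on which section is read.

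The stated unit also suits a trial with fixed arms and equal follow-up better than it suits this study. Group membership depends on what happens during follow-up. A child who begins TKM in month 8 and is placed in the combination group on one-year information brings seven months of events from before any TKM into that group. Under a six-month classification the same child would be a conventional-treatment child, and any later events on TKM would count there if the whole study period is used. Nor does a yes/no per child reflect how long the child was observed.

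What is at stake is whether the safety comparison describes harm under TKM, or partly describes length of follow-up and timing of uptake.

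**Working it through.** **The plan's own figure.** No safety rate or safety sample size is stated. The only figure to reproduce is the efficacy sample size: "Using a 2-sided test, a sample size of approximately 37 children per treatment would assure 80 % power". With difference 1.6 and SD 2.2, n = 2 × [2.2 × (1.960 + 0.842) / 1.6]² = 29.68 per group, and 29.68 / 0.8 = 37.1. Two treatments by four subgroup cells gives 8 × 37 = 296 to 8 × 38 = 304, against 300 stated. It reproduces, but has no bearing on safety.

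**Inputs.** Follow-up of 12 months and dropout of 0.2 come from the article. Every event rate below is an assumption.

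**1. Length of follow-up.** Let each child have non-serious events at a constant rate r per year, equal in both groups. The chance of being counted after t years is 1 − exp(−r·t). With r = 1:

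- 12 months: 1 − exp(−1) = 63%
- 6 months: 1 − exp(−0.5) = 39%
- a group losing 20% at month 6: 0.8 × 0.632 + 0.2 × 0.393 = 58%

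If one group loses 20% at month 6 and the other loses nobody, the comparison is 58% against 63%, a ratio of 0.584 / 0.632 = 0.92, with no true difference. Swapping the groups reverses the direction. If both lose children in the same pattern, no false difference arises.

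**2. Events before exposure.** With r = 1 throughout and TKM begun after seven months, the chance of an event before any TKM is 1 − exp(−7/12) = 44%. The chance over the whole year is 63%. So about 0.442 / 0.632 = 70% of such children who are counted already had an event before exposure.

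**3. Sensitivity when events are frequent.** Share of children with at least one event in a year:

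| Rate per child-year | Poisson, 1 − exp(−r) | Negative binomial, dispersion 1, 1 − 1/(1+r) |
|---|---|---|
| 0.1 | 9.5% | 9.1% |
| 0.5 | 39% | 33% |
| 1 | 63% | 50% |
| 2 | 86% | 67% |
| 4 | 98% | 80% |
| 6 | 99.8% | 86% |

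The share exceeds 85% only from about 2 per child-year (Poisson) or about 6 (dispersion 1).

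Power for an assumed rate ratio of 1.5, with 120 completers per group (300 / 2 × 0.8, assuming equal groups) and two-sided α of 0.05. For the rate analysis, power = Φ[ln 1.5 / √v − 1.96], where v = (1/r + 1/(1.5r)) / 120 under Poisson, plus 2/120 with dispersion 1. The participant analysis compares two proportions.

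| Rate per child-year | Poisson: participants vs rate | Dispersion 1: participants vs rate |
|---|---|---|
| 0.1 | 18% vs 19% | 16% vs 18% |
| 0.5 | 55% vs 68% | 33% vs 49% |
| 1 | 69% vs 93% | 34% vs 64% |
| 3 | 41% vs about 100% | 25% vs 79% |

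At 0.1 per year the two analyses are equivalent. The loss appears as the rate rises.

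**The case against.** Counting participants with at least one event is a standard safety summary. The two specific sections agree on it, and the Study design sentence may be loose overview wording. The safety paragraph also promises to report the course of serious events and to apply a liver-injury causality scale for long-term medication, so safety reporting is not confined to a yes/no. Exposure-adjusted rates may sit in a full protocol or SAP that is not shown. The late switcher follows from the group definition, which affects every outcome.

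Much of this stands, and it limits the point. The participant count is not an error and should be kept. But the article does more than omit detail: it fixes both the outcome and its analysis, in a design where exposure and follow-up vary by child, and gives two units. That the group definition also affects other outcomes does not remove its effect here.

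Two stronger readings are tempting and unsupported.

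- A reader might infer that the non-serious count must approach a ceiling because most young children will report something within a year. The article gives no event rate. At 0.1 to 0.5 events per child-year the share is about 9% to 39%, which is no ceiling, and clustering of events within children lowers it further.
- A reader might infer that the assumed 20% dropout will itself make TKM look safer. The article does not say that dropout differs by group. The 0.92 ratio requires loss in one group only, and could favour either.

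**Conclusion.** The point holds in this form. The article is inconsistent on whether events or children are counted. The child-level count, as written, can assign events from before TKM exposure to the TKM group and makes no allowance for unequal follow-up.

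The possible size, assuming 1 event per child-year, is 39% of children counted over 6 months against 63% over 12. One-sided loss of 20% at month 6 would give a false ratio of about 0.92. Reduced sensitivity of the participant count is a conditional further risk, confined to frequent non-serious events; it is not an argument about rare serious events. The inconsistency of unit and the lack of any allowance for exposure timing and follow-up can be read from the text; the sizes rest on assumed rates.

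**What to change.** 1. **Reconcile the unit** across Study design, Secondary outcome measurement, and Statistical and analytical plans. State that both participants with events and numbers of events will be reported.
2. **Keep the participant count** for serious and non-serious events.
3. **Add a rate for non-serious events** per child-month observed, by Poisson or negative binomial regression with log child-months as offset and standard errors clustered by child. If serious events are few, report simple exposure-adjusted rates rather than a model.
4. **Split events and time at first TKM exposure**, using the monthly treatment surveys. In the main safety analysis, count everything after first exposure as TKM-exposed.
5. **Use current on/off-TKM month only as a sensitivity analysis.** As a main analysis it could credit delayed harm, or harm that led to stopping, to off-TKM time.

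The surveys already collect what is needed, so the cost is wording and one more model. There are two small downsides: repeat reports of one continuing event must be merged by a stated rule, and results will depend to some degree on the attribution window chosen. Both should be fixed before analysis.
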